Shenmai (BL62)	On the lateral side of the foot, in the depression directly below the tip of the lateral malleolus
Zhaohai (KI6)	On the medial side of the foot, in the depression on the inferior border of the medial malleolus, vertically below the apex of the medial malleolus

Treatment will be administered three times per week on alternating days for 6 consecutive weeks. Standardized medication tapering interviews will be conducted prior to weekly acupuncture sessions.

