### Outcome measures

#### Primary outcome measures

The successful discontinuation rate at the end of the 6-week treatment was defined as the proportion of patients who had completely ceased NBZDs use (any dose) during the final week of treatment (days 36–42). Medication adherence was verified using patients’ daily diaries and medication records. Patients completed a daily diary card, on which they recorded the date, medication name, dose, time of administration, and any adverse reactions. The diary cards were returned to the physician at each weekly visit, and prescription records were cross-checked by an independent observer every 3 weeks. Any discrepancy between the diary and medication records will be resolved by consensus of two blinded independent investigators based on all available data (daily diaries, medication records). Urine or blood drug concentration testing was not performed to confirm participants’ self-report of hypnotic discontinuation, due to the short half-life of NBZDs (requiring daily sampling, which is logistically infeasible) and the increased participant burden that would likely raise dropout rates. The multi-source adjudication approach described above was considered a reliable alternative.

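### The check that replaces drug testing cannot show whether tablets already held were taken on days 36–42, so calling it reliable is too strong

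*Protocol article*

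**What the plan says.** All of the key text is in the protocol article, Primary outcome measures.

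- **Endpoint.** Success is the proportion who had "completely ceased NBZDs use (any dose) during the final week of treatment (days 36–42").
- **Sources.** "Medication adherence was verified using patients’ daily diaries and medication records". The diary card is completed by the participant each day and handed in at each weekly visit. The term medication records is not defined.
- **External check.** "prescription records were cross-checked by an independent observer every 3 weeks".
- **Adjudication.** "Any discrepancy between the diary and medication records will be resolved by consensus of two blinded independent investigators", who decide "based on all available data (daily diaries, medication records").
- **No assay.** Urine and blood testing are ruled out because of the sampling that a short half-life would need and because of the burden on participants.
- **The article's own assessment.** "The multi-source adjudication approach described above was considered a reliable alternative".

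Other sections give the context. Participants enter after more than 6 months of NBZD use, with at least one failed attempt to stop and a wish to reduce (Inclusion criteria). The dose then falls by 25% of baseline per week, with weekly in-person consultations and twice-weekly calls (NBZDs tapering protocol). Study limitations does not mention this aspect of outcome measurement.

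**The concern.** The endpoint is all-or-nothing over seven days, so a single unrecorded dose turns a failure into a success. What matters is whether the verification step can contradict a diary that leaves out such a dose.

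A prescription record documents supply, not intake. After more than 6 months of use and with a falling dose, it is plausible that some participants hold tablets at home, although the article neither shows this nor rules it out. A participant who takes one of those tablets and does not record it leaves two sources that agree. Adjudication begins only when the sources disagree, so blinding the adjudicators does not help in this case.

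At stake are the level of both discontinuation rates and, depending on how misreporting is spread over the arms, the difference between them. The secondary NBZDs reduction rate is also calculated from weekly dose, so it shares the weakness where that dose comes from the diary.

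**Working it through.** **Step 1: what each source can reveal.** The table sets out the possible cases for days 36–42, using the sources that the article describes.

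| What happened | Diary | Prescription record | Result |
|---|---|---|---|
| No use | none | no new supply | success, correct |
| Use, recorded | dose entered | either | failure, correct |
| Use from new supply within the checked records, not recorded | none | new supply | discrepancy, adjudicated |
| Use of tablets already held, not recorded | none | no new supply | success, wrong |

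The first and last rows produce identical data, so no adjudication rule applied to these two sources can separate them. The third row shows that the check does have some value.

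**Step 2: illustrative size.** The documents give no misreporting rate. Let f be the assumed share of true failures recorded as successes. Take p = 50.00% (electroacupuncture) and 10.83% (sham) from Sample size, treated here as true rates.

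Recorded rate = p + f(1 − p). With equal f in both arms:

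difference = (1 − f)(0.5000 − 0.1083) = (1 − f) × 0.3917

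| f (assumed) | Electroacupuncture | Sham | Difference (points) | Power, 32 per arm |
|---|---|---|---|---|
| 0 | 50.0% | 10.8% | 39.2 | 94% |
| 10% | 55.0% | 19.7% | 35.3 | 85% |
| 20% | 60.0% | 28.7% | 31.3 | 72% |
| 30% | 65.0% | 37.6% | 27.4 | 60% |

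Power is from the normal approximation for two proportions, two-sided α = 0.05, at the article's 32 evaluable per arm. There is no continuity correction, so the first row lies above the planned 90%. The trend is the point, not the level.

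**Step 3: unequal misreporting.** With shares f₁ (electroacupuncture) and f₀ (sham):

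difference = 0.3917 + f₁(0.5000) − f₀(0.8917)

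- f₁ = 20%, f₀ = 10%: 0.3917 + 0.1000 − 0.0892 = 0.4025, or 40.3 points, above the true 39.2.
- f₁ = 10%, f₀ = 20%: 0.3917 + 0.0500 − 0.1783 = 0.2634, or 26.3 points, below it.
- No true effect (10.83% in both arms), f₁ = 20%, f₀ = 10%: recorded rates are 28.7% and 19.7%. The chance of a significant result favouring electroacupuncture is about 13% at 32 per arm, against a nominal 2.5% in that direction. Swapping the shares gives the same chance in favour of sham.

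**Step 4: can existing visits support a second source?** Under Acupuncture procedure, "Treatment will be administered three times per week on alternating days for 6 consecutive weeks". Three alternate-day sessions span five days (for example 36/38/40 or 38/40/42), so they cannot fall on both day 36 and day 42. The weekly visits, at which diary cards are already returned, are the better place.

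**The case against.** The other side has several good points.

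- **The sources are not limited to prescriptions.** A reader might infer that the diary is compared with prescription records and nothing else. The article does not say so. It also names medication records without defining them, and the full protocol may say more. What the text supports is that prescription records are the only external source described.
- **It is not wholly unverified self-report.** A reader might call it that, but a new prescription that contradicts the diary can be caught.
- **Leftover stock is not shown.** The article is silent on quantities supplied and on return of unused drug, and a condensed article may leave these out. Such stock is plausible, not documented.
- **The omission of assays is explained.** It is a disclosed and reasoned design choice, and this point does not challenge it.
- **The illustration may double count.** The 50% and 10.83% are themselves observed rates. If they were based on self-report, they already contain some misreporting.
- **A bias in favour of electroacupuncture is not established.** A reader might infer one. Participants are to be blinded, blinding is assessed three times with a sensitivity analysis if it fails, and expectancy is measured at baseline. Equal misreporting shrinks the difference. A spurious benefit needs unequal misreporting.
- **A tablet count can be evaded.** Someone who conceals a dose can also under-declare stock.

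All of these stand, and they limit the scope and size of the point. They do not rescue the statement of reliability. That statement concerns a procedure that the article itself describes, and the procedure cannot detect use of tablets already held.

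**Conclusion.** The point holds in a limited form. For an any-dose endpoint over days 36–42, the described verification can detect contradictory new supply but not unrecorded use of tablets already held. Such use raises no discrepancy, so it is never adjudicated. Describing the approach as a reliable alternative to testing is therefore overstated. This is a weakness in a stated rule, not a detail left to another document.

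The magnitude is unknown. The figures of 35.3, 31.3 and 27.4 points against 39.2 rest on an assumed f of 10%, 20% and 30%, equal in both arms, and on treating the planning rates as free of misreporting. Under unequal misreporting the difference could move either way. The documents support neither a particular value of f nor a particular direction. The gap is worth closing because doing so is cheap, not because bias has been shown.

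**What to change.** In Primary outcome measures:

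1. At baseline, record all NBZD tablets that the participant declares holding.
2. At each existing weekly visit, reconcile tablets held and newly supplied against the returned diary card. Include the visit closest to the start of week 6 and the visit at which the card for days 36–42 is returned. These need not fall exactly on days 36 and 42. The count is compared with the diary doses over the same interval.
3. Treat any unexplained shortfall over an interval that spans days 36–42 as a discrepancy, and send it to the two blinded adjudicators already in place.
4. State what medication records means.
5. Replace the reliability sentence with a description of the outcome as diary-based, with prescription-record and tablet reconciliation.

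In Study limitations, state that undeclared tablets, whether home stock or obtained elsewhere, remain undetected.

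The cost is one line on the weekly case report form, a short amendment and minor inconvenience in bringing tablets to visits. No assay, extra visit or additional staff is needed, and dosing and taper are untouched. For participants who have already passed week 6, counts cannot be recovered, but the corrected wording and the limitation still apply.

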#### Secondary outcome measures

Secondary outcomes are assessed at baseline, during treatment, and during follow-up. Detailed assessment procedures are provided in the Supplementary Appendix S1; assessment time points are summarized in Table 1.

(1) *Subjective Sleep Scales*

① Consensus Sleep Diary (CSD): Records total sleep time (TST), sleep onset latency (SOL), wake after sleep onset (WASO), sleep efficiency (SE), subjective sleep quality, and medication use (32–35).

② Insomnia Severity Index (ISI): 7-item scale (0–28) (36); scores ≥15 indicate clinically significant insomnia (37); a reduction of ≥8 points indicates meaningful improvement (38).

③ Pittsburgh Sleep Quality Index (PSQI): Global sleep quality (0–21); scores > 5 indicate poor sleep quality (39–42).

(2) *Daytime Functioning Assessment*

① Epworth Sleepiness Scale (ESS): Daytime sleepiness across eight situations (43, 44).

② Fatigue Severity Scale (FSS): 9-item scale (9–63); scores ≥36 indicate clinically significant fatigue (45–47).

③ Generalized Anxiety Disorder 7-item Scale (GAD-7): Anxiety severity (0–21) (48–50).

④ Patient Health Questionnaire-9 (PHQ-9): Depression symptom severity (51, 52).

(3) *Medication Reduction Response Assessment*

① NBZDs Reduction Rate

The NBZDs reduction rate was calculated using the following formula: NBZDs reduction rate = (Pre-treatment weekly NBZDs dose - Post-treatment weekly NBZDs dose) / Pre-treatment weekly NBZDs dose * 100% (Note: Pre-treatment refers to the baseline period, and post-treatment refers to week 6 of the treatment period) (16).

② Benzodiazepine Hypnotics Withdrawal Symptom Scale (BHWSS): 12-item self-report (3-point scale) assessing withdrawal symptoms (53, 54).

③ Medication Craving Visual Analogue Scale (VAS): 0–10 scale (0 = no craving, 10 = extreme craving) (55).

(4) *Objective sleep assessment parameters*

① Polysomnography (PSG): performed as the primary objective sleep assessment, with all participants undergoing one night of 8-h monitoring during screening to exclude other sleep disorders; sleep stages and parameters were manually scored according to the AASM Manual (Version 3.0) (56–58).

② Actigraph (ACT): Recorded for 7 consecutive days at baseline and at the end of intervention; parameters included number of awakenings (NOA), total wake time (TWT), sleep onset latency (SOL), total sleep time (TST), and sleep efficiency (SE) (59–62).

Objective sleep measures (PSG and ACT) were not collected at the 10-week follow-up because the primary focus of this trial was NBZDs discontinuation, not direct sleep improvement. To enhance patient convenience and retention, some participants will be followed up online (video/phone) at week 10, precluding in-person objective measurements. PSG is resource-intensive and burdensome, and actigraphy requires prolonged device wear, both of which could increase dropout rates in this pragmatic feasibility study.

(5) *Assessment of acupuncture treatment expectancy*

The Acupuncture Expectancy Scale (AES) is a four-item instrument rated on a 5-point Likert scale, yielding total scores ranging from 4 to 20 (63). The AES evaluates participants’ pretreatment expectations regarding acupuncture intervention, with higher scores indicating greater expectancy. Scores >12 indicate high expectancy, whereas scores ≤12 indicate low expectancy (64). The AES was administered once prior to treatment initiation.

(6) *Blinding assessment*

Blinding effectiveness will be evaluated by asking participants whether they perceived needle penetration during treatment. Assessments will be conducted at three time points: baseline (after the first treatment session), mid-term (end of week 3), and final (end of week 6, after the last treatment session). Participants will also be asked to guess their group assignment (electroacupuncture, sham, or unsure) and to rate their confidence level. The blinding index will be calculated at each time point. If systematic unblinding is detected, sensitivity analyses will be performed excluding participants who correctly guessed their assignment with high confidence.

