### Inclusion criteria

Participants must meet all of the following criteria:

(1) Aged 18–65 years, regardless of sex;(2) Meeting the diagnostic criteria for chronic insomnia according to ICSD-3TR;(3) Participants were required to have insomnia symptoms of mild to moderate severity (Insomnia Severity Index ≤ 21) while taking NBZDs (25);(4) Continuous use of NBZDs for chronic insomnia for more than 6 months, with medication adherence exceeding 50% of the treatment period and a dosing frequency of at least three nights per week during the 2 weeks prior to screening;(5) Use of NBZDs recommended in the Chinese Guideline for the Diagnosis and Treatment of Insomnia in Adults (2023 edition), with each dose not exceeding the guideline-recommended maximum (18);(6) Self-reported history of at least one unsuccessful attempt to discontinue NBZDs independently;(7) A clear willingness to reduce NBZDs dosage;(8) No history of acupuncture or other needle-based therapies within the past 6 months;(9) Ability and willingness to comply with the study protocol and provision of written informed consent.

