### NBZDs tapering protocol

Based on the 2025 European clinical practice guideline recommending a gradual dose reduction of 10–25% per week for NBZDs (27), and supported by two clinical studies that successfully employed a weekly 25% reduction strategy (21, 28), NBZDs will be reduced at a rate of 25% of the baseline dose per week. If participants experience intolerable withdrawal symptoms during tapering—such as exacerbation of insomnia, anxiety, or agitation—the dose will be temporarily reverted to the previous level. Tapering will be reattempted during the subsequent evaluation cycle (1 week per cycle).

Throughout the treatment period, participants will attend weekly in-person consultations and receive twice-weekly telephone follow-ups. Dose adjustments will be conducted through a shared decision-making process, enabling participants to actively engage in symptom monitoring and self-management under physician supervision. Final dosage modifications will require investigator approval.

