### Concomitant medication

Throughout the study period, participants will not be permitted to use any additional pharmacological treatments that may affect sleep, mood, or autonomic function, including antidepressants, anxiolytics, antipsychotics, melatonin, and melatonin receptor agonists.

Medications prescribed for stable chronic medical conditions (e.g., hypertension, diabetes, or dyslipidemia) will be allowed, provided that the dosage has remained unchanged for at least 4 weeks prior to enrollment and throughout the study period.

Any temporary or emergency medication use will be documented in detail, including the drug name, dosage, duration, and indication, and will be considered in subsequent analyses if necessary.

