### Efficacy evaluation criteria

① Primary Efficacy Outcome Measures

The primary efficacy outcome is the successful discontinuation rate of NBZDs at the end of the 6-week treatment period. Between-group differences in discontinuation rate will be evaluated using regression-based methods appropriate for binary outcomes.

② Secondary Efficacy Outcome Measures

a. Subjective Sleep Efficacy Evaluation

Subjective sleep outcomes, including the Insomnia Severity Index (ISI) and Pittsburgh Sleep Quality Index (PSQI), will be analyzed using longitudinal mixed-effects models incorporating repeated measurements across predefined study time points to estimate treatment effects over time.

b. Objective Sleep Efficacy Assessment

Objective sleep parameters derived from PSG and ACT will be analyzed using longitudinal mixed-effects models to account for within-subject correlation and to evaluate changes across study time points.

c. Daytime Functioning Assessment

Daytime functioning outcomes will be analyzed using longitudinal mixed-effects models to assess treatment effects across time.

d. NBZDs Reduction Response Evaluation

Medication reduction responses, including NBZDs reduction rate, withdrawal symptoms, and craving scores, will be evaluated using regression-based models appropriate to outcome type, with longitudinal modeling applied where repeated measurements are available.

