### Sample size

The expected discontinuation efficacy rate for the sham acupuncture group in the sample size calculation was derived from a randomized controlled trial that enrolled 144 long-term benzodiazepine users (21). However, this trial yielded a negative result, which might be attributable to the simultaneous inclusion of both BZDs and NBZDs in the study medication (22). Therefore, only the sham acupuncture group discontinuation rate of 10.83% was adopted from that trial, while the expected successful discontinuation rate for the acupuncture group was based on our pilot study.

A pilot study was conducted at our center prior to the main trial to assess the feasibility of the intervention and to obtain preliminary estimates of effect size. Ten eligible patients with chronic insomnia disorder who had used NBZDs regularly for >6 months received electroacupuncture (three times per week for 6 weeks) combined with the standardized 6-week NBZD tapering protocol (25% dose reduction every week). The successful discontinuation rate was 50.00% (5/10). No serious adverse events were reported. Detailed pilot study results are provided in Supplementary Appendix S2.

Based on expected outcomes and relevant published literature (21), this study hypothesized that after treatment, the discontinuation efficacy rates of NBZDs at 6-week post-treatment for the electroacupuncture group and sham needle and sham electroacupuncture group would be 50.00 and 10.83%, respectively. This study set *α* = 0.05 and 1-*β* = 0.90, employing a two-sided test with equal sample sizes between treatment and control groups. Referencing the sample size estimation formula for comparing efficacy rates between two groups from Sun Zhenqiu’s Medical Statistics, the calculation formula was as follows:

$$n=1641.4/{\left[\frac{\left(u_{\alpha }+u_{\beta }\right)}{\sin^{-1}\sqrt{P_{1}}-\sin^{-1}\sqrt{P_{2}}}\right]}^{2}$$

where 
$u_{\alpha }$
=1.96 (for 
α
=0.05, two-sided), 
$u_{\beta }$
=1.282 (for 
β
=0.10), P_1_ = 50.00%, and P_2_ = 10.83%. The calculation yields n = 31.7 ≈ 32 cases. Accounting for dropout rates, the clinically set dropout rate is 20%, resulting in a final sample size of 39 participants per group, totaling 78 participants across both groups.

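### The PSQI global score partly overlaps with the primary outcome: on standard scoring, stopping NBZDs lowers it without any change in sleep, by up to about 1.18 points between arms at week 10

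*Protocol article*

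**What the plan says.** Under Secondary outcome measures, the Protocol article lists among the subjective sleep scales "Pittsburgh Sleep Quality Index (PSQI): Global sleep quality (0–21); scores > 5 indicate poor sleep quality". Table 1 schedules it at baseline, week 6 and week 10. Under Efficacy evaluation criteria, in the part on subjective sleep, the article states: "Subjective sleep outcomes, including the Insomnia Severity Index (ISI) and Pittsburgh Sleep Quality Index (PSQI), will be analyzed using longitudinal mixed-effects models".

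Inclusion criterion 4 requires "Continuous use of NBZDs for chronic insomnia for more than 6 months, with medication adherence exceeding 50% of the treatment period" together with "a dosing frequency of at least three nights per week during the 2 weeks prior to screening". The primary outcome is complete cessation of NBZDs, at any dose, on days 36–42. Under Concomitant medication, "participants will not be permitted to use any additional pharmacological treatments that may affect sleep, mood, or autonomic function", so a participant who stops NBZDs should normally be taking no sleeping medication at all.

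The article does not name the PSQI components, set any component apart, or comment on overlap between this scale and the primary outcome. It refers detailed assessment procedures to Supplementary Appendix S1, which is not shown.

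**The concern.** A sleep scale used in a deprescribing trial should not move merely because the drug was stopped. The PSQI global score, as usually scored, counts sleeping-medication use as one of its seven components. This trial recruits people at the top of that component and then tests whether one arm stops the drug more often. Any success on the primary outcome therefore lowers the PSQI total in that arm, even if nobody sleeps better.

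Randomisation does not remove this, because the shift follows treatment success. The mixed model does not remove it either, because the shift is part of the score being modelled. What is at stake is interpretation: part of a between-arm PSQI difference could be reported as better sleep when it only restates that more participants stopped. In an individual who stops, real worsening of up to 3 points could be offset in the total. The problem is greatest at week 10, when PSG and actigraphy are not collected and the sleep evidence is self-report only.

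**Working it through.** The plan states no expected PSQI difference or SD, so there is no planned figure to reproduce. The arm sizes are taken as stated.

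**Inputs from the Protocol article**
- Discontinuation rates (Sample size): rates in the electroacupuncture group and the "sham needle and sham electroacupuncture group would be 50.00 and 10.83%, respectively".
- Arm size (Sample size): 32 per arm before dropout, 39 after.
- Entry use (Inclusion criteria): at least three nights per week in the 2 weeks before screening. If adherence above 50% over more than 6 months is read as nights, it means more than 0.5 × 7 = 3.5 nights per week on average.
- Taper (NBZDs tapering protocol): "NBZDs will be reduced at a rate of 25% of the baseline dose per week".

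**Assumptions not in the documents**
- Standard PSQI: seven components of 0 to 3. This agrees with the stated range, since 7 × 3 = 21.
- One component scores past-month use of sleeping medication: 0 for none, 1 for less than once a week, 2 for once or twice a week, 3 for three or more times a week.
- PSQI SD of 3 to 4.

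**Step 1, baseline.** Use on three or more nights per week scores 3. The recent-use criterion covers 2 weeks and the recall one month, but the long-term criterion closes most of that gap. Nearly all participants start at 3.

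**Step 2, week 10.** Recall covers weeks 7–10. A participant who stopped and stayed off scores 0, a fall of 3 of 21 points (14%). If all others stay at 3:
- electroacupuncture: 3 × 0.50 = 1.50 points
- sham: 3 × 0.1083 = 0.32 points
- built-in difference: 3 × (0.50 − 0.1083) = 3 × 0.3917 = 1.18 points

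**Step 3, week 6.** Recall covers weeks 3–6. On the fastest taper (first cut in week 1, zero dose in week 4), a nightly user has 7 nights of use in 28. That is 7/4 = 1.75 per week, score 2, a fall of 1. The built-in difference is 1 × 0.3917 = 0.39 points. It depends on the pattern of use:
- If last use is in week 4, there are 14 nights in 28, or 3.5 per week. The score stays at 3 and there is no fall.
- A participant dosing three nights a week on the fastest taper has 3 nights in 28, or 0.75 per week. The score is 1, a fall of 2. If every stopper were like this, the difference would be 2 × 0.3917 = 0.78 points.

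**Step 4, chance of p<0.05 with no sleep effect.** Two-sample t-test, two-sided 5%, as a stand-in for the model's group contrast at one visit. Noncentrality = difference / (SD × √(2/n)), with 2n − 2 degrees of freedom. For example, at week 10 with SD 3 and n = 39: 1.18 / (3 × √(2/39)) = 1.18 / 0.68 = 1.73.

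| Visit, difference | n per arm | SD 3 | SD 3.5 | SD 4 |
|---|---|---|---|---|
| Week 10, 1.18 | 39 | 0.40 | 0.31 | 0.25 |
| Week 10, 1.18 | 32 | 0.34 | 0.26 | 0.21 |
| Week 6, 0.39 | 39 | 0.09 | 0.08 | 0.07 |
| Week 6, 0.39 | 32 | 0.08 | 0.07 | 0.07 |

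The nominal value is 0.05 throughout. With the medication component left out, the built-in difference is 0.

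**The case against.** The strongest objection is that the article never describes the PSQI components, and that scoring detail may sit in Supplementary Appendix S1. This stands in part: the point depends on the labelled assumption of standard scoring. However, the main text commits to a 0–21 global score, which is the full seven-component total. A score without the medication component would run 0–18. The point is therefore about something stated, not about an omission.

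A second objection is that 1.18 points is a best case for the concern. This stands. It applies at week 10 only, and the documents give no relapse rate after treatment. Participants who do not fully stop but move to intermittent use would also score lower. There are more of them in the sham arm, so the gap would narrow. With the planned dropout the chance of a spurious result is also lower. At week 6, when the primary outcome is assessed, the effect is small.

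Some stronger readings are tempting, but the documents do not support them:
- That PSQI simply repeats the primary outcome. Only one component of seven overlaps.
- That the cut-off above 5 distorts a result. It is given as description, and no analysis uses it.
- That worse sleep after withdrawal would go unseen. ISI, the sleep diary and the withdrawal symptom scale run to week 10, PSG and actigraphy are done at week 6, and the diary records medication use as an item separate from its sleep parameters. A PSQI fall without matching changes in these would be visible.

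**Conclusion.** The concern holds as a partial overlap between one secondary sleep scale and the primary outcome. On standard PSQI scoring, the plan builds in a difference favouring electroacupuncture that needs no change in sleep. It is at most about 1.18 points at week 10 and about 0.39 at week 6. The chance of p<0.05 from this alone is about 0.21–0.40 at week 10 and 0.07–0.09 at week 6.

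These figures rest on the planned discontinuation rates, 32 to 39 per arm and an assumed SD of 3 to 4. The week-10 figure also needs stoppers to stay off the drug and others to stay at the component maximum. The week-6 figure describes nightly users on the fastest taper.

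The primary test and sample size are unaffected. The ISI, diary, PSG and actigraphy sleep parameters do not share the artefact. A reader might infer that the trial's sleep evidence as a whole is compromised, but that does not follow. The change is a cheap improvement to how one secondary outcome is interpreted, best made before results are known.

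**What to change.** Under Secondary outcome measures and Efficacy evaluation criteria, state that between-arm PSQI inference about sleep uses the sum of the six components without sleeping medication (0–18). Report the standard 0–21 global score alongside for comparability, and state that a difference in it will not by itself be read as a sleep benefit. Do not carry the cut-off above 5 over to the six-component sum.

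The cost is a line of scoring and analysis wording. The standard questionnaire already collects the items, so no new data are needed. The small downside is less direct comparability with published global scores, which the parallel report preserves.
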